### Study setting

The study is carried out from 2008 to 2010 in an integrated primary care setting, by the patient's own GP, pharmacist and practice nurse if available. All Dutch GPs, practice nurses and pharmacists working in primary care will be informed about the study and invited to participate by mail, by websites, by several articles in pharmacy and GP journals and by several presentations at regional meetings or at national symposia. They are asked to cooperate as a group of at least one pharmacist and at least two GPs. This cooperation includes sharing data from electronic medical records required for the study. The GPs are allocated as an intervention GP or a control GP, by random selection.

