### Randomisation

Cluster randomisation takes place after informed consent of the participating GPs and pharmacists on a GP level and before the selection of patients. For every pharmacist a random selection of the intervention GP is made. The other participating GP becomes the GP who will include control patients.

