Data from the digital Excel CRF and from a Microsoft Access database are combined and further analysed by using R, version 2.6.2. In R mixed-effects Cox models[22] are designed to study the effect of the intervention on hospital admissions related to medication and the effect on survival, quality of life and adverse drug events. All available patient data are included. The pharmacist and the GP are integrated as random effects in the models. P-values < 0.05 are regarded as statistically significant. The two-sided 95% bootstrap percentile confidence intervals are computed using 1000 replications. Bootstrap samples are obtained by random sampling GP's or patients with replacement from the population. To assess the model's goodness of fit we create plots of outcome versus follow-up time, versus number of diseases and examined residuals. The influence of the baseline characteristics such as age, gender, number of physicians, number of diseases, number of drug prescribed, refill rate and follow-up time are also analysed using linear mixed-effects models or generalized linear mixed-effects models.

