This study also has some limitations. First, selection bias may occur by just including patients who are willing to cooperate in the intervention. However, the same selection will take place in the control group because they also have to cooperate in completing the questionnaires. Second the selection of the participating pharmacist and GPs is based on voluntary participation. Only motivated couples of GPs and a pharmacist who established a good cooperation will participate in the study, which hampers the generalizability. But in case the intervention shows an effect, these participating GPs and pharmacists can be a role model for their colleagues in the region. A third limitation is the extensive and therefore demanding intervention. It is thinkable that it will not be implemented as described in the protocol because this is not possible or feasible in daily practice. A fourth limitation is the selection of intervention and control patients on a general practice level but from the same pharmacy which implies that control patients are cared for by the same pharmacist as the intervention patient. This possibly leads to contamination bias, but we do not expect that the pharmacist will provide other care than usual care to the control patients. A fifth limitation is the assessment of the ADEs which will be done by the patient's own pharmacist and GP who are not blinded to the assignment to intervention or control group. Knowing to which group the patient is assigned, may possibly affect their judgement of ADEs, which can potentially lead to the detection of more ADEs in the control group. On the other hand an advantage may be that they know their patients so they can make a better judgement if the symptoms are related to the medication or to a disease.

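### The bootstrap rule permits resampling of individual patients in a trial that randomises GPs, so the reported 95% intervals can be too narrow

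*Protocol article*

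**What the plan says.** All references are to the protocol article.

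- **Interval method (Data analysis).** "The two-sided 95% bootstrap percentile confidence intervals are computed using 1000 replications". The next sentence gives the sampling unit: "Bootstrap samples are obtained by random sampling GP's or patients with replacement from the population". It does not say which unit goes with which model, and it does not offer the pharmacy as a unit.
- **Model (Data analysis).** "The pharmacist and the GP are integrated as random effects in the models". Significance is declared at a p-value below 0.05. The text does not say that this p-value is derived from the bootstrap.
- **Design (Randomisation).** "Cluster randomisation takes place after informed consent of the participating GPs and pharmacists on a GP level and before the selection of patients". Allocation is made inside each pharmacy: "For every pharmacist a random selection of the intervention GP is made. The other participating GP becomes the GP who will include control patients".
- **Shared pharmacist (Discussion).** The limitations confirm that "control patients are cared for by the same pharmacist as the intervention patient".
- **Group size (Study setting).** "They are asked to cooperate as a group of at least one pharmacist and at least two GPs". Two GPs per pharmacy is therefore a minimum.

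**The concern.** A bootstrap interval has the right width only if the resampling copies the way independent units entered the trial. Here patients sit within GPs, GPs sit within pharmacies, and treatment is contrasted between GPs of the same pharmacy. The model recognises both levels; the resampling sentence allows a scheme that recognises neither.

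Drawing patients one by one treats them as independent. The chance that the intervention GPs simply had better or worse patients or habits than their control partners then drops out of the interval. This is the usual unit-of-analysis error of cluster trials, and it makes the result look more precise than it is.

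The bootstrap is the only interval method the protocol states, so the reported precision of the treatment effect depends on this sentence. A patient-level interval could also disagree with the p-value of a model that does carry the cluster effects.

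**Working it through.** **Inputs.** From Sample size: 50 patients per GP, 142 pharmacies, 284 GPs, 7100 patients per arm, 1% event rate, 50% reduction, alpha 0.05, power 0.80. The protocol gives no ICC and no split of variance between GP and pharmacy, so both are assumed and varied.

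**Step 1: a plausible ICC.** The plan gives no interval width to reproduce; its one relevant figure is 7100 per arm. The usual formula for 1% against 0.5% (two-sided 0.05, power 0.80, no clustering) gives 4673 per arm, not 7100. The ratio is 7100/4673 = 1.519. Setting 1 + (50 − 1) × ICC = 1.519 gives ICC = 0.519/49 = 0.0106. This is a back-calculation used only to choose a working value. With a continuity correction (5065 per arm) it would be 0.0082, and one-sided (3681 per arm) 0.0190.

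**Step 2: variance under each scheme.** Let ρ be the total ICC, f the share of it at pharmacy level, and total variance 1. Per GP pair, up to a common factor:

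- Correct (the pharmacy effect cancels within the pair): ρ(1 − f) + (1 − ρ)/50
- GP resampling (the pharmacy effect returns): ρ + (1 − ρ)/50
- Patient resampling: 1/50 = 0.02

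Relative width is the square root of the ratio to the correct variance. Coverage is 2Φ(1.96 × relative width) − 1.

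**Step 3: numbers at ρ = 0.0106.** Here (1 − ρ)/50 = 0.019788, and the GP-resampling variance is 0.0106 + 0.019788 = 0.030388.

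| Clustering at pharmacy level | Correct variance | Patient resampling: width (coverage) | GP resampling: width (coverage) |
|---|---|---|---|
| None | 0.030388 | √(0.02/0.030388) = 0.811 (88.8%) | 1.000 (95.0%) |
| Half | 0.0053 + 0.019788 = 0.025088 | √(0.02/0.025088) = 0.893 (92.0%) | √(0.030388/0.025088) = 1.101 (96.9%) |
| All | 0.019788 | √(0.02/0.019788) = 1.005 (95.1%) | √(0.030388/0.019788) = 1.239 (98.5%) |

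Patient intervals are too narrow once the GP-level variance exceeds 1/49 of the pharmacy-level variance, which is almost any GP-level variation. The ratio of the two permitted widths is √(0.02/0.030388) = 0.81 whatever the split.

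**Step 4: range.** Over assumed ICCs of 0.005 to 0.05 and all splits, patient-level width runs from 0.54 to 1.03 times correct and GP-level width from 1.00 to 1.91.

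**Step 5: simulation.** Both simulations used the crude log rate ratio with 142 pairs and 50 patients per GP.

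- First: 1% against 0.5%, 600 trials, 300 draws each, seven settings of pharmacy and GP variation. Coverage was 89–96% for patient resampling (width 0.84–1.02 of correct), 94–98% for GP resampling (0.95–1.20) and 92–95% for whole-pharmacy resampling (0.95–1.04). The low end for pharmacies, 91.7%, came from one setting with equal variation at both levels, where patient resampling gave 90.5% and GP resampling 93.7%.
- Second: 1% rate, between-GP coefficient of variation 1.0, 1,000 trials, 400 draws each. Patient resampling covered 87%, 91%, 90% and 94% with 0, 25, 50 and 75% of the variance at the pharmacy. GP resampling covered 94–97% and pharmacy resampling 94–96%.

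**The case against.** **GP resampling is not wrong in the same way.** A reader might infer that neither permitted unit fits and that the intervals must therefore have the wrong width. The protocol does not support that. The GP is the randomised unit, so GP resampling matches the level of allocation and misses only the pairing. It is exact if pharmacies do not differ and otherwise conservative. Without clustering, both options are right. This stands.

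**The trial's error rate is not shown to change.** A reader might take 88.8% coverage to mean a false-positive rate of about 11%. It is non-coverage of a reported interval under assumed inputs. The significance rule follows the description of a model with both random effects and is not tied to the bootstrap. This stands.

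**The size rests on assumptions.** The ICC is back-solved, and the 0.81 figure needs all clustering at GP level. A smaller ICC or more pharmacy-level variance reduces the shortfall; a larger ICC increases it. The figures also concern crude comparisons. A refitted model with a pharmacist effect would still adjust for pharmacy wherever both GPs of a pair are drawn, so the excess width under GP resampling may not carry over. This stands, which is why a range is given.

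**The choice may be settled elsewhere.** The article is condensed, and an analysis plan may say which unit goes with which model. A reader might infer that the width could be chosen after seeing the data; that cannot be concluded from this document alone. But permission to resample patients is a stated rule, not an omitted detail. Every comparison between arms comes from the same GP-randomised design, so resampling patients alone suits none of them. This part of the objection fails.

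**Conclusion.** The point holds for the patient-level option. In a trial that randomises GPs within pharmacies, resampling patients alone understates the uncertainty of the treatment effect as soon as GPs of the same pharmacy differ more than trivially. At a total ICC of 0.0106 the reported intervals would have between 0.81 and about 1.0 of the correct width, with 89% to 95% coverage, depending on how much of the clustering is at pharmacy level. Both the ICC and that split are assumptions, and the arithmetic is for crude comparisons rather than the mixed-effects Cox estimate.

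The GP-level option is valid to conservative: it can cost precision but does not inflate error. The consequence is confined to the reported intervals. This should be fixed, but it does not by itself undermine the trial's stated test of significance.

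**What to change.** Delete patients as a permitted resampling unit and replace the sentence with:

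*Bootstrap samples are drawn by sampling pharmacies with replacement, each with all its participating GPs and all their patients; repeated draws of a pharmacy and its GPs are relabelled as distinct clusters and the mixed model is refitted in each sample.*

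Referring to all participating GPs matters because a pharmacy may have more than two. Relabelling matters because a pharmacy drawn twice would otherwise be fitted as one larger cluster, which distorts the random effects.

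The cost is one sentence. It needs no new data and no change to the model, and computing time is about the same.

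### Follow-up time is listed as a baseline characteristic in the supplementary mixed models, and baseline covariates are named only for those models, none for the Cox model that estimates the intervention effect

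*Protocol article*

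**What the plan says.** All the modelling text is in one paragraph of the protocol article, under Data analysis.

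- Intervention effect: "mixed-effects Cox models[22] are designed to study the effect of the intervention on hospital admissions related to medication", with the same models used for the secondary outcomes. On further terms the text says only this: "The pharmacist and the GP are integrated as random effects in the models".
- Model checking: follow-up time appears in "plots of outcome versus follow-up time, versus number of diseases and examined residuals".
- Covariates: "The influence of the baseline characteristics such as age, gender, number of physicians, number of diseases" opens a list that ends with "number of drug prescribed, refill rate and follow-up time are also analysed using linear mixed-effects models or generalized linear mixed-effects models".

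Three other sections bear on this. Participants plans 12 months of follow-up and withdraws patients who leave the participating GP or pharmacist, including by a move to a nursing home, or who withdraw consent. Outcomes makes survival a secondary outcome. Randomisation says "Cluster randomisation takes place after informed consent of the participating GPs and pharmacists on a GP level", and places this step ahead of patient selection.

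**The concern.** A baseline characteristic is fixed at or before inclusion. Age, gender, number of diseases, number of drugs and refill rate at inclusion meet that test; follow-up time does not. Its length is decided after allocation by death, relocation, nursing-home admission or withdrawal, any of which the intervention could influence. In the Cox models it is already the time axis. If it also enters another model as an ordinary covariate beside treatment, that model conditions on something that may itself be a consequence of treatment, and its coefficients lose their plain meaning.

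The second part concerns where the genuine baseline variables are used. The article attaches them to the supplementary models and names none for the Cox model. GPs are randomised, but patients are chosen and consented afterwards, so the arms can differ in measured risk in a way that randomising GPs does not prevent. The Discussion itself accepts that selection through willingness to cooperate may occur.

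**Working it through.** The plan gives no figure for this point, so there is none to reproduce. The check is a comparison of the texts, followed by two labelled illustrations.

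**1. Is each listed variable known at inclusion?**

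- Age, gender, diseases, drugs: yes. Table 5 marks age, gender, chronic conditions and dispensing data as obligatory items.
- Refill rate: yes. Table 1 computes it for eligibility from the preceding 12 months.
- Follow-up time: no. It is known only when the patient's observation ends.

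**2. Could follow-up time depend on outcome or treatment?** Yes. Participants and Outcomes together give death, nursing-home moves, relocation and withdrawal as ways in which observation ends early. The article does not say whether follow-up also ends at the first admission, or whether follow-up time is meant as a covariate, an offset or a descriptive factor.

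**3. How much could it matter if used as a covariate?** This is an illustration, not a prediction.

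- From the protocol (Sample size): 1% of controls admitted and a 50% reduction, used as yearly rates of 0.01 and 0.005.
- Assumed: control death rate 0.06 per year; a frailty shared by admission and death (gamma, mean 1, variance 0.5); mortality either unaffected or 30% lower under intervention; no clustering.
- Size: 5 × 7,100 = 35,500 per arm, 30 replications.
- Model: logistic regression for any admission before death or 12 months, on treatment alone and then on treatment plus follow-up time.

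| Follow-up ends at | Mortality under intervention | OR without follow-up time | OR with | Ratio |
|---|---|---|---|---|
| death or 12 months | unaffected | 0.495 | 0.495 | 1.00 |
| death or 12 months | 30% lower | 0.504 | 0.501 | 0.99 |
| first admission, death or 12 months | unaffected | 0.503 | 0.495 | 0.98 |
| first admission, death or 12 months | 30% lower | 0.508 | 0.615 | 1.21 |

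The last row has a simple explanation. If follow-up stops at admission, anyone with less than 12 months was either admitted or died. Among them the odds of admission against death are 0.01/0.06 = 0.167 in controls and 0.005/(0.06 × 0.7) = 0.119 under intervention. The ratio is 0.119/0.167 = 0.71, which is 0.5/0.7. Exact conditioning on follow-up time would thus pull the estimate from 0.5 towards 0.71; a single linear term gave 0.615. With mortality unaffected the same arithmetic gives 0.5/1 = 0.5, in line with the small change in the third row.

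**4. What could a measured imbalance do to an unadjusted hazard ratio?** The inputs are all assumed. With a 2-year difference in mean age and a hazard rising 5% per year of age, the shift is 1.05² = 1.10. At 3% it is 1.03² = 1.06, and at 8% it is 1.08² = 1.17.

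Chance alone would not produce such a gap. With an assumed age SD of 7 years, an assumed intracluster correlation of 0.05 and 50 patients per GP, the design effect is 1 + 49 × 0.05 = 3.45. The standard error of the difference is 7 × √(2 × 3.45/7,100) = 0.22 years. A 2-year gap would need recruitment to differ between arms.

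**The case against.** The strongest reply is that the paragraph says less than a critical reader may take from it. Three stronger readings are tempting, and the article supports none of them.

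- A reader might infer that the primary estimate is unadjusted. The article neither lists nor excludes fixed covariates for the Cox model. The covariate sentence adds an analysis and takes nothing away from the Cox model, and a condensed article may leave the list to a fuller document. An unadjusted primary model would also be a legitimate choice in a randomised trial.
- A reader might infer that the treatment effect is certainly conditioned on follow-up time. The text says only that the influence of these characteristics is analysed. An offset would be possible within the generalised linear mixed models already named, and nothing places follow-up time as a covariate in the primary model.
- A reader might infer that the effect could be removed or reversed. The illustration showed neither. One of four scenarios gave a material attenuation, and it needed two conditions that the article does not state.

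Safeguards against differential recruitment also count. Eligibility rests on criteria taken from dispensing and age data, and computer selection applies when too many patients qualify. An average pharmacy has about 450 eligible patients against the 100 sought. Each pharmacist is paired with an intervention and a control GP.

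All of this stands, and it confines the point to supplementary models and a cheap safeguard. It does not make follow-up time a baseline characteristic; that is an error in the printed text, not an omission. The recruitment safeguards limit clinician choice but not differences in consent. The patient's own pharmacist, who serves both arms, seeks consent after allocation. The Discussion expects equal selection because controls also complete questionnaires, yet describes the intervention as demanding.

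**Conclusion.** The point holds as a minor one. Follow-up time is misclassified as a baseline characteristic, and its role in the supplementary models is undefined. Used as a covariate it may distort those models. In the illustration the change was 2% or less in three scenarios and 21% on the odds-ratio scale in the fourth. These figures rest on assumed death rates, frailty and mortality effects, and on a definition of follow-up that the article does not give.

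Separately, the article names baseline covariates for the supplementary models and none for the Cox model, in a design where patients enter after allocation. That supports a recommendation to pre-specify adjustment; it is not a finding that the primary estimate is biased or unadjusted. The 6% to 17% age illustration shows scale only, because both the age gap and the gradients are assumed.

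**What to change.** 1. Delete follow-up time from the list of baseline characteristics. Use it only as the time axis in Cox models and as a log offset in any count model, and state when follow-up ends for each outcome.
2. State in advance that the primary mixed-effects Cox model is adjusted for age, gender, number of diseases, number of drugs and refill rate, all as measured at inclusion, and report the unadjusted model alongside. If a fuller plan already fixes this list, a one-line reference to it is enough.

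The cost is a few sentences of analysis text. The variables are already collected in the CRF or computed for eligibility, so no new data are needed and neither the sample size nor the conduct of the trial changes.

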## Discussion

The PHARM-study looks into the effect of the complex pharmaceutical care process on medication related hospital admissions. This patient centred pharmaceutical care process is highly patient individualized, includes several steps (figure 1) and is conducted in a primary care setting. This care process can only be partly structured in a study protocol because it is dependent on patients' autonomy, the performance of the clinicians and on the cooperation between them. These issues cannot be completely restrained to a protocol and will be a reflection of real clinical practice. In the PHARM-study the effectiveness of the pharmaceutical care process will be studied in daily clinical practice and due to this the study is a pragmatic trial. Such a trial is suitable to evaluate effectiveness rather than to measure efficacy[30].

A key methodological issue in pragmatic trials is balancing internal and external validity[30]. This issue is addressed for the PHARM-study in the study design and evaluation protocol. External validity, or generalizability, is achieved by allowing the GPs and the pharmacists to implement the intervention in their own manner within their daily practice. External validity is also addressed by having very few exclusion criteria and general inclusion criteria. The included high-risk patients are a heterogeneous group, with multiple and varying morbidities and medication usage. Internal validity is maintained by selecting intervention patients from another general practitioner than the control patients, to reduce contamination bias by ensuring that GPs do not apply strategies and knowledge used in the intervention patients to control patients.

We expect this study to have several other strengths besides internal and external validity. First, we have gained experience during several previous pilot projects and because of this we were able to optimize the intervention by providing a structure for the pharmacotherapy review. We have also optimized the CRF for documentation of the pharmaceutical care and the planned intervention in drug therapy to guarantee the continuity of care. Since pharmacotherapy and medical services become more complex, creating a comprehensive documentation is required to facilitate collaboration between members of the health care team and ensure continuity of care. Second, the pharmacist and the GP are offered a training regarding the study protocol, the documentation and how to perform a structured pharmacotherapy review. A third strength is the large group of patients, which makes it possible to measure a possible effect on medication related hospitalisations. A fourth strength is the extensive intervention during a period of 12 months in an interdisciplinary setting in cooperation between the patient and the own GP and pharmacist, which makes it more likely to solve all major drug therapy problems.

This study also has some limitations. First, selection bias may occur by just including patients who are willing to cooperate in the intervention. However, the same selection will take place in the control group because they also have to cooperate in completing the questionnaires. Second the selection of the participating pharmacist and GPs is based on voluntary participation. Only motivated couples of GPs and a pharmacist who established a good cooperation will participate in the study, which hampers the generalizability. But in case the intervention shows an effect, these participating GPs and pharmacists can be a role model for their colleagues in the region. A third limitation is the extensive and therefore demanding intervention. It is thinkable that it will not be implemented as described in the protocol because this is not possible or feasible in daily practice. A fourth limitation is the selection of intervention and control patients on a general practice level but from the same pharmacy which implies that control patients are cared for by the same pharmacist as the intervention patient. This possibly leads to contamination bias, but we do not expect that the pharmacist will provide other care than usual care to the control patients. A fifth limitation is the assessment of the ADEs which will be done by the patient's own pharmacist and GP who are not blinded to the assignment to intervention or control group. Knowing to which group the patient is assigned, may possibly affect their judgement of ADEs, which can potentially lead to the detection of more ADEs in the control group. On the other hand an advantage may be that they know their patients so they can make a better judgement if the symptoms are related to the medication or to a disease.

The PHARM-study is one of the largest controlled trials to study the effect of the total pharmaceutical care process, including a pharmaceutical anamnesis, followed by a pharmacotherapy review, a pharmaceutical care plan, monitoring and follow up evaluation of pharmacotherapy, in an ordinary integrated primary care setting on medication related hospital admissions. Few controlled trials in this area have been performed and none have investigated the extensive intervention of the total pharmaceutical care process, performed in cooperation of the patient, the pharmacist, the GP and the practice nurse, in this group of high risk patients, at the scale of this study either in terms of the number of practices or the number of patients. The PHARM-study should provide evidence as to whether such a pharmaceutical care process should be implemented in a primary care setting in the Netherlands.
